### Qualitative interviews

Following the establishment of the child’s IHP, individual interviews will be conducted with a selection of children, parents and healthcare professionals involved in the care planning discussions from both cohorts. These interviews will explore their perspectives and insights on the concept of participation, the child’s involvement in the actual needs assessment process and strategies for promoting participation. This includes discussing the specific support provided by healthcare professionals to enhance participation.

### Data management

Each of the participating children will be assigned a unique identifying number that will be used to establish a link between the various data collection forms, including parental and healthcare professionals’ questionnaires. All collected data will be stored pseudonymously in a dedicated research data storage area designed to meet stringent requirements for handling sensitive personal information. This storage solution is integrated into a centralised file server system, ensuring redundancy, backup and secure access controls. Participant confidentiality will be rigorously upheld, with stringent measures in place to prevent unauthorised access to the data.

### Data analysis plan

Descriptive statistics will be used to summarise the sociodemographic characteristics of the children and their families. The questionnaires will be analysed using inferential statistical analysis such as t-test and analysis of variance, whereas associations between variables will be analysed by correlation and multiple regression. Multiple imputation will be used to handle missing data. The individual interviews will be transcribed verbatim and then analysed with inductive content analysis as described by Graneheim and Lundman.^20^ Document analysis of excerpts of the children’s IHP’s will be performed with quantitative content analysis according to Krippendorf^21^ and qualitative content analysis as described by Graneheim and Lundman,^20^ with a focus on descriptions of formulated goals. Trial findings will be reported according to CONSORT 2010 guidelines.^22^ The SPIRIT reporting was used for this submission.^23^

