**Trial registration number:**

NCT06381856.

STRENGTHS AND LIMITATIONS OF THIS STUDYUser involvement will be a key aspect.The study will contribute to our understanding of how to enhance the participation of autistic children and adolescents in their healthcare.Mixed methods will be used, analysing quantitative and qualitative data from the participating children, parents/guardians and healthcare professionals.This will be a non-randomised observational study with limited possibility for causal inferences.The study will focus on children with autism spectrum disorder, so the findings may not be generalisable to children with other disabilities.

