### Aim

The primary aim is to investigate the effect of two needs assessment models on children’s participation in the needs assessment process from the child’s, parent’s and professional’s perspective. The secondary aim is to investigate the association of perceived participation with mental health, QoL and formulation of goals in the child’s IHP.

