## Methods and analysis

### Study design

The study is a prospective observational study comparing responses from children and parents who underwent a survey-based assessment procedure to responses from those who instead had a meeting-based assessment procedure.

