#### Measures

*Background questions*. A set of eight sociodemographic questions concerning the child and the family.

*Your child’s strengths, abilities and special needs*. This questionnaire, adapted from the Family Outcome Survey,^14^ aims to gather insights into parents’ understanding of their child’s profile. Parents respond on a 5-point Likert scale ranging from ‘Nothing/Never’ to ‘Everything/Always’. Two versions are available: one with four questions for use before needs assessment meetings and another with five questions for use after the final meeting or for the survey-based group after the needs assessment completion. This questionnaire is completed solely by parents.

*Perceived collaboration with the neuropsychiatric team*. Comprising five questions, this questionnaire assesses the family’s interaction with the neuropsychiatric team at the CYHC and the child’s involvement during these interactions. Responses are provided on a 5-point Likert scale. This questionnaire is completed solely by parents.

*The Mental Health Continuum-Short Form(MHC-SF)*.^15^ This questionnaire consists of 14 questions rated on a 6-point Likert scale, measuring mental health across three domains: emotional, psychological and social well-being. The MHC-SF has been validated from 7 years of age in Portuguese speaking children^16^ and from 12 years of age in Swedish speaking children.^17^ In the present project, three versions are available: one where the child self-reports, one where the parent self-reports and one where the parent assesses the child’s mental health (proxy assessment).

*Cantril ladder*.^18^ This tool evaluates QoL using a visual representation of a ladder numbered from 0 (lowest QoL) to 10 (highest QoL) in a valid and reliable manner.^19^ It is completed solely by the children.

*The child’s involvement*. This questionnaire contains seven to nine questions regarding participation and engagement during needs assessment meetings. It is available in three versions: one for the child, one for the parent and one for the healthcare professional. Each version has two variants tailored for regular meetings and the closing meeting. Responses are rated on a 4-point Likert scale ranging from ‘Not at all’ to ‘Very much’.

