## Discussion

This article outlines the rationale and design of the study, detailing the recruitment process, the content of the needs assessment procedures, the outcome measures and the quantitative and qualitative data analyses. If successful, the study will yield insights into the effects and efficacy of enhancing the participation of autistic children in the habilitation process. It will also shed light on the obstacles and enabling factors for implementing needs assessment procedures in healthcare settings.

The strengths of the study lie in its user involvement in both design and result interpretation, the provision of detailed profiles for individual children and families and the utilisation of a mixed-methods approach incorporating quantitative and qualitative data from children, parents and healthcare professionals. However, a methodological limitation is the observational design, which restricts the ability to draw causal inferences. Moreover, as the study will be conducted in a single region in Sweden with a focus on children with ASD, the findings may not be directly generalisable to children in other countries or with different disabilities. Nonetheless, it is reasonable to infer that other autistic children may share similar needs and could derive comparable benefits from enhanced participation in the habilitation process. Finally, children’s understanding of participation is likely to vary with age, with older children demonstrating more advanced reasoning. However, the instruments used for this study have already been tested in a previous study involving children within the same age range. To further capture the children’s voices and perceptions, we will conduct interviews, allowing them to express their own views on what participation means to them and how they felt they were able to participate in the assessment process.

In conclusion, if the study achieves its objectives, it has the potential to enhance children’s participation in their care, thereby potentially improving their mental health and QoL. This, in turn, could lead to reduced need for support and service from healthcare providers.

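### The non-randomised cohort comparison is planned with t-test or analysis of variance, with no stated adjustment for age or the collected background items

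*Protocol article*

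**What the plan says.** All references are to the protocol article.

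- **Design.** The strengths and limitations box (under the trial registration number) states: "This will be a non-randomised observational study with limited possibility for causal inferences". Study design describes "comparing responses from children and parents who underwent a survey-based assessment procedure to responses from those who instead had a meeting-based assessment procedure".
- **Aim.** "The primary aim is to investigate the effect of two needs assessment models on children’s participation in the needs assessment process". The present study and the Discussion also speak of efficacy.
- **Method.** The Data analysis plan says: "The questionnaires will be analysed using inferential statistical analysis such as t-test and analysis of variance". The same sentence then assigns, by way of contrast, correlation and multiple regression to associations among variables. That matches the secondary aim, which concerns how perceived participation relates to mental health, quality of life and goal formulation.
- **Covariates.** Measures lists "A set of eight sociodemographic questions concerning the child and the family", without naming the items. The one use given for them in the Data analysis plan is a descriptive summary.
- **Age.** Eligibility runs from 7 to 17 years. The Discussion expects understanding of participation to differ with age, with "older children demonstrating more advanced reasoning". Its answer is that the instruments were tested earlier in the same age range and that interviews will be held.
- **Size.** Participants and sample size gives 60 children per group for d = 0.5, 80% power and 5% alpha.

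**The concern.** Without randomisation, nothing makes the two cohorts alike in age or family background. A t-test takes no covariates, and analysis of variance is named here without any. The one listed method that could adjust is directed to another question. If the cohorts differ on a measured variable that is related to the involvement score, the planned contrast carries that difference and the report would present it as part of the effect of the procedure.

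The primary conclusion is at stake. The bias can go either way: it can produce a difference where none exists, or hide one that does. Acknowledging that causal inference is limited does not remove the part of the bias that variables already held could reduce.

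**Working it through.** **1. The plan's own figure.** Inputs from Participants and sample size: d = 0.5, 80% power, 5% alpha (two-sided assumed, since sidedness is not stated).

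- n per group = 2(1.960 + 0.842)² / 0.5² = 62.8, so 63 (normal approximation); 64 with the t distribution.
- Power at 60 per group = Φ(0.5·√30 − 1.960) = Φ(0.779) = 78.2%; 77.5% with the t distribution.

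The stated 60 is a near miss. It corresponds to a plain two-group comparison of means with no allowance for covariates. The small shortfall is a separate matter, and the present point does not depend on it.

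**2. Bias of the unadjusted contrast.** Take one covariate with within-cohort correlation r to the outcome and a difference between cohorts of m SD. With no true effect:

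- spurious d = r × m
- standard error of d at 60 per group ≈ √(2/60) = 0.183
- false-positive rate = 1 − Φ(1.960 − d/0.183) + Φ(−1.960 − d/0.183)

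The article gives neither r nor m. The values below are assumed and span mild to strong.

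| r | m (SD) | spurious d | share of target 0.5 | false-positive rate |
|---|---|---|---|---|
| 0.1 | 0.1 | 0.01 | 2% | 5.0% |
| 0.3 | 0.2 | 0.06 | 12% | 6.2% |
| 0.3 | 0.3 | 0.09 | 18% | 7.8% |
| 0.3 | 0.5 | 0.15 | 30% | 13.0% |
| 0.5 | 0.3 | 0.15 | 30% | 13.0% |
| 0.5 | 0.5 | 0.25 | 50% | 27.8% |

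The same shift can mask a difference. With a true d of 0.5 and a bias of −0.25, the apparent d is 0.25. The chance of a significant result is then 27.8% in place of 78.2%.

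**3. What adjustment does to power.** Let R² be the outcome variance explained by the covariates and R²g the share of cohort membership that they explain (both assumed). The effective SD is s = √((1 − R²)/(1 − R²g)), and power at 60 per group is Φ(0.5·√30/s − 1.960).

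| R² | R²g | power at 60 per group | n per group for 80% |
|---|---|---|---|
| 0 | 0.10 | 73.8% | 70 |
| 0.10 | 0.10 | 78.2% | 63 |
| 0.20 | 0.10 | 82.8% | 56 |
| 0 | 0.20 | 68.8% | 79 |

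Adjustment may cost or gain a little power, depending on whether the covariates relate more to cohort or to outcome. The case for adjustment rests on bias and not on precision.

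**The case against.** The strongest reply is that the sentence on methods introduces its examples with an open phrase, covers many questionnaires and reporters, and sits in one condensed paragraph of a journal article. A covariate list could properly stand in an analysis plan that is not shown. Regression is planned somewhere, and the limitation is disclosed. Part of this stands: the article does not forbid adjustment, and the missing list of covariates is no fault. But it does name a method class for the comparison, and its contrast sends regression elsewhere. The point concerns what the article fixes, not what it omits.

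Four stronger readings are tempting, and the documents do not support them.

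- *Age is a known predictor of the primary outcome.* The Discussion speaks of understanding of participation, not of involvement scores. Age also confounds only if the cohorts differ in age. With one centre, one set of eligibility criteria and consecutive invitation, no age gap is shown.
- *The unadjusted test wastes precision.* The second table in the working shows that this need not be so.
- *Baseline well-being is available for adjustment.* The text gives no pre-assessment time point for the MHC-SF or the Cantril ladder, and Figure 1 is not shown. Adjusting for a post-assessment value would condition on a secondary outcome.
- *The planned reporting guideline confirms the absence of adjustment.* The article says "Trial findings will be reported according to CONSORT 2010 guidelines", but what that guideline or an alternative requires lies outside the documents, and no weight is placed on it here.

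**Conclusion.** The concern holds as a weakness that should be fixed. The article names unadjusted methods for the questionnaire comparison, assigns regression to another aim and gives the background items only a descriptive role, while the primary aim is to "investigate the effect of two needs assessment models". Followed as written, this leaves measured case-mix differences in the primary contrast.

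The size is not known. The range of 0.01 to 0.25 in d, and of about 5% to 28% in false-positive rate, depends wholly on assumed correlations and imbalances and on a single covariate. At the mild end the harm is negligible; at the strong end it is half the target effect. It is a risk, not a demonstrated bias.

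**What to change.** - Make the primary cohort comparison a prespecified linear regression (ANCOVA) of the child-reported involvement score on cohort, adjusted for age and a short prespecified set of the collected background items.
- Add the MHC-SF or Cantril value only if it is measured before the needs assessment.
- Report the adjusted difference with its 95% confidence interval as primary and the unadjusted t-test as supportive.
- Word the aim as an adjusted comparison of the two procedures, in place of effect or efficacy.

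**Cost.** Age and the background items need no new data collection. The change is one of wording plus a few degrees of freedom, with possibly slightly lower power if the covariates relate more to cohort than to outcome; hence the short list. No precision gain should be claimed. Confounding from unmeasured factors, calendar time and selective response (about 30% of eligible children are expected to take part) would remain, so the stated limitation on causal inference should stay.

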### Participants and sample size

To be eligible for participation in the study, a child or adolescent must be aged 7–17 with a diagnosis of ASD without intellectual disability. No other exclusion criteria will be applied. A power analysis was conducted based on results obtained from pilot testing of items in the Child Involvement Questionnaire (the primary outcome). This analysis determined that 60 children would be required in each group, totalling 120 children, to detect a moderate effect size difference between groups (Cohen’s d=0.5) with 80% power and a 5% alpha level. Since the main focus of the study is on children’s participation, no power calculation was conducted for the number of parents or staff involved. Given an expected intake of eligible children ranging from 300 to 400 per year at the CYHC and assuming a response rate of about 30% (based on experience from previous studies at the CYHC), the data collection period is estimated to be approximately 1 year.

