#### Meeting-based needs assessment

In the meeting-based assessment, families are provided with comprehensive information about the CYHC and then contacted to schedule four meetings. These meetings take place at the CYHC and involve the child, one parent and a healthcare professional such as an occupational therapist or a special needs educator. Depending on the child’s age and the arrangements made, the parent may participate throughout the entire meeting or during specific segments.

The purpose of the first meeting is to establish a connection with the therapist, to create an alliance and to allow the child to acclimate to the new environment, understand the diagnosis, feel heard and leave with a positive experience. The second meeting delves deeper into the child’s experience and preferences for meetings, necessary adaptations and activities. In the third meeting, the therapist provides insight into autism and its impact on brain function and then engages the child in discussion about their experience of stress and of maintaining energy balance over time. In line with these discussions, the therapist may also suggest activities aimed at promoting overall well-being. The fourth meeting focuses on summarising the child’s autism profile, identifying their needs and prioritising treatments based on appropriateness rather than simply availability of professionals. Each meeting typically lasts between 30 and 45 min.

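### The named tests and the sample size treat children as independent, although meeting-cohort children very likely share professionals; if they do and the ICC is above 0, the naive standard error is too small

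*Protocol article*

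**What the plan says.** The Data analysis plan says that the questionnaires will be analysed by "inferential statistical analysis such as t-test and analysis of variance, whereas associations between variables will be analysed by correlation and multiple regression". It mentions no term for the professional.

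Participants and sample size states that "60 children would be required in each group, totalling 120 children". The target difference is Cohen's d=0.5, and the power and significance level are set at 80% and 5%. No allowance for clustering is stated, and "no power calculation was conducted for the number of parents or staff involved".

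The two cohorts differ in how the assessment is delivered. Under Meeting-based needs assessment, families are "then contacted to schedule four meetings", and these "involve the child, one parent and a healthcare professional such as an occupational therapist or a special needs educator". The same section adds: "The purpose of the first meeting is to establish a connection with the therapist, to create an alliance". Under Survey-based needs assessment, a team of professionals assesses the questionnaires that the family returns.

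The primary outcome is the perception of participation (Abstract). The involvement questionnaire exists in child, parent and professional versions (Measures). Data management links all forms through the child's number and does not mention an identifier for the professional.

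**The concern.** A t-test or a one-way ANOVA assumes that each child's score is independent of every other child's in the same group. In the meeting cohort the experience being scored is created in person by a professional, in part through an alliance. Two children seen by the same professional may therefore give more similar scores than two children seen by different ones. The survey procedure has no meeting professional, so for the child-rated score this source of dependence sits in one cohort only, which makes the design partially nested.

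If the dependence exists and is ignored, the interval for the primary difference is too narrow and the test rejects too often. A difference produced by one or two particularly skilled professionals could then be read as an effect of the assessment model. The professional-rated score has a further source of dependence, because one rater may score several children. The article's aim includes the professional's perspective, so this score matters too.

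**Working it through.** **Inputs from the article.** 60 children per group, d=0.5 (SD set to 1), 5% alpha, 80% power, one centre. Sidedness is not stated; two-sided is assumed.

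**Inputs assumed, because the article does not give them.** Number of professionals k = 4 to 15, so m = 60/k = 15 to 4 children each, equally shared. ICC by professional = 0.01 to 0.10. Total variance is equal in both cohorts.

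**Step 1: the article's own figure.** With independent children, a two-sided test at d=0.5 and 80% power needs 63 per group (normal approximation) or 64 (t). At 60 per group the power is 78.2% (normal) or 77.5% (t). So 60 is slightly short before any clustering, and under a two-sided test it contains no hidden allowance for clustering. That shortfall is a separate matter; here it only supplies the baseline.

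**Step 2: standard error with clustering in the meeting cohort only.**

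- Design effect in the meeting cohort: DE = 1 + (m − 1) × ICC
- Naive SE = √(2/60) = 0.183
- True SE = √((1 + DE)/60)
- SE ratio = true/naive = √((1 + DE)/2)
- Actual two-sided type I error of the naive test ≈ 2 × [1 − Φ(1.96/ratio)]

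| Professionals (k) | m | ICC | DE | SE ratio | Type I error |
|---|---|---|---|---|---|
| 15 | 4 | 0.01 | 1.03 | 1.007 | 5.2% |
| 4 | 15 | 0.01 | 1.14 | 1.034 | 5.8% |
| 15 | 4 | 0.05 | 1.15 | 1.037 | 5.9% |
| 6 | 10 | 0.05 | 1.45 | 1.107 | 7.7% |
| 4 | 15 | 0.05 | 1.70 | 1.162 | 9.2% |
| 15 | 4 | 0.10 | 1.30 | 1.072 | 6.8% |
| 4 | 15 | 0.10 | 2.40 | 1.304 | 13.3% |

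At ICC = 0, or with 60 different professionals, the ratio is 1.00 and the error rate stays at 5%. A ratio of 1.304 means that the true SE is 30% larger than the naive one. Equivalently, the naive SE is 1 − 1/1.304 = 23% too small.

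**Step 3: what a correct analysis costs (k = 6, ICC = 0.05).**

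- True SE = √(2.45/60) = 0.202
- Satterthwaite df = (1 + DE)² / [DE²/(k − 1) + 1/59] = 2.45² / [1.45²/5 + 1/59] = 6.00/0.437 = 13.7
- Critical t = 2.15, against 1.98 with 118 df
- Interval width relative to the naive one = 1.107 × 2.15/1.98 ≈ 1.20
- Noncentrality = 0.5/0.202 = 2.47; power from the noncentral t ≈ 63%, against 77.5% without clustering

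The normal approximation would give 69.7% here; the rest of the loss comes from the few degrees of freedom. With k = 4 and ICC = 0.10 the df falls to about 6 and the interval is about 60% wider.

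**The case against.** The strongest reply is one of scope. The article is a condensed account, its list of methods opens with such as, and it assigns no test to the primary outcome. A random effect or a cluster-robust standard error could be specified in a fuller plan. This stands to the extent that the text does not rule out an adjustment. It does not dispose of the point: the group comparisons that are named assume independence, and so does the sample size. If no form records the professional, no later plan can repair the analysis.

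The second reply is that the premises are inferred. This also stands in part:

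- A reader might infer that the article says each professional runs meetings for several children. It does not. Sharing is very likely, because avoiding it would take about 60 professionals for 60 children at one centre, but it remains an inference.
- A reader might infer that one professional sees a child throughout. The alliance wording suggests continuity without fixing it.
- A reader might conclude that the standard errors are certainly too small. That needs an ICC above 0 and shared professionals, and the documents give figures for neither. At ICC 0.01 the effect on the SE is only about 1% to 3%.
- A reader might infer that nesting is absent from the survey cohort for every outcome. Data collection and instruments refers to questionnaire variants by cohort and by respondent, professionals included, so professional raters may be shared in both cohorts.
- Silence on a professional identifier under Data management does not show that none is collected; the forms are not shown.

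**Conclusion.** The point holds in conditional form. The named group comparisons and the sample size make no allowance for clustering by professional in the meeting cohort, where clustering is plausible and sharing of professionals is close to unavoidable. If professionals are shared and the ICC is above 0, the naive analysis understates uncertainty. The size ranges from negligible to serious according to two quantities that the article does not report, so no single figure can be claimed. The range in the table rests on equal caseloads, equal variances and a normal approximation. The documents do not support the statement that the nominal 5% level will be broken, only that nothing stated protects it. The change is worth making now, because the identity of the professional may not be recoverable after data collection.

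**What to change.** 1. Record on the forms which professional led each child's meetings, and report the number of professionals and children per professional.
2. Compare the cohorts on the involvement score with a partially nested mixed model: a random professional effect in the meeting cohort only, with Satterthwaite or Kenward-Roger degrees of freedom. The small-sample correction is essential if professionals are few.
3. If several professionals see the same child, use the lead professional or a multiple-membership term.
4. For professional-rated scores, add a random rater effect in whichever cohorts share raters.
5. Restate the power of 60 per group under a declared range of professionals and ICC.

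**Cost.** One identifier field and a different model statement. Statistically, the intervals widen by the amounts in the working, more so with fewer professionals. The variance between professionals will be imprecisely estimated when they are few, so its estimate should be reported with that caution.
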